##### Short-form McGill Pain Questionnaire

The McGill Pain Questionnaire is a multi-dimensional tool for pain assessment, for its qualitative description of pain, its publication in 1975 represented a major evolution in pain research [53]. The short-form McGill Pain Questionnaire (SF-MPQ) is a shorter version of the original MPQ and was developed later in 1987 [54], composing of three components. The first one is the pain rating index, which has 2 subscales: a sensory subscale with 11 words, and an affective subscale with 4 words from the original MPQ. These words or items are ranked on an intensity scale as 0 = none, 1 = mild, 2 = moderate, and 3 = severe. The second one is a 10-cm visual analogue scale (VAS) for average pain, and the third one is for present pain intensity [55], which are rated as 0 = no pain, 1 = mild, 2 = discomforting, 3 = distressing, 4 = horrible, and 5 = excruciating.

#### Other observation indicators

##### Patent's satisfaction with the efficacy of treatment

Including: Extremely satisfied, satisfied, average, dissatisfied, extremely dissatisfied.

##### Safety evaluation

Adverse effects, including humeral shaft fracture, glenoid fracture, shoulder dislocation, complex regional pain syndrome, neurovascular lesions, and infection, will be recorded at any time during the trial. In addition, an MRI of the glenohumeral joint and a musculoskeletal ultrasound of the shoulder will be performed 6 months after treatment to assess the safety effects of the MUA on the rotator cuff.

### Participant timeline {13}

Patients with FS will be randomly divided into the trial group and the control group. All patients included in this study will receive their disseminated treatment on Day 1 and undergo a program of shoulder exercises, for 2 weeks. The relevant data will be collected before the intervention, 1 day, 2 weeks, 4 weeks, 12 weeks, and 24 weeks after the intervention, while safety evaluations and adverse events will be recorded each visit. The specific participant’s timeline is shown in Table 1.

**Table 1 Tab1:** Participant’s timeline

Timepoint (state unit)	−7~0 DAY	Treatment day	1 day	2 weeks	4 weeks	12 weeks	24 weeks
Visit number:	1	2	3	4	5	6	7
Enrollment:							
Eligibility screen	x						
Informed consent	x						
Allocation	x						
Imagining examination	x						x
Baseline questionnaire	x						
Interventions:							
Intra-articular steroid injection		x					
Manipulation under anesthesia		x					
2-week shoulder exercises			x	x			
Assessments:							
Active range of motion		x	x	x	x	x	x
Passive range of motion		x	x	x	x	x	x
CMS		x	x	x	x	x	x
MPQ		x	x	x	x	x	x
VAS		x	x	x	x	x	x
PPI		x	x	x	x	x	x
Total effectiveness rate							x
Safety evaluation		x					x
Adverse event		x					x

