### Safety/harms {22}

Throughout the trial, it is necessary to monitor and record any adverse events and reactions. If adverse events occur, such as negative impacts on patients' consciousness, emotions, physical activity, sleep, blood pressure, heart rate, respiration, upper limb fractures, skin damage, nerve injury, bleeding, and black stools, they will be documented thoroughly on the case report form. This documentation should include the time, severity, duration, and treatment measures, as well as an analysis of the correlation between the adverse reaction and the experimental treatment method, considering any complications and concurrent treatments. The clinical observe physician can decide to halt the trial if the patient's condition warrants it. Any patients who discontinue treatment due to adverse reactions should be closely monitored and investigated, with detailed records of the results.

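### Table 1 marks safety evaluation and adverse events only at treatment day and 24 weeks, while the text of the same section requires them at every visit

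*Protocol article*

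**What the plan says.** Three places in the Protocol article describe ongoing recording of harms:

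- Participant timeline {13}, text: "safety evaluations and adverse events will be recorded each visit".
- Safety evaluation (under Outcomes {12}): listed adverse effects "will be recorded at any time during the trial".
- Safety/harms {22}: "Throughout the trial, it is necessary to monitor and record any adverse events and reactions".

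The visits are fixed in the same timeline section: "The relevant data will be collected before the intervention, 1 day, 2 weeks, 4 weeks, 12 weeks, and 24 weeks after the intervention". That text then refers the reader to Table 1 for the participant's specific timeline.

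Table 1 has seven visit columns: screening, treatment day, 1 day, and 2, 4, 12 and 24 weeks. Its last two rows, for safety evaluation and "Adverse event", each carry two marks, at treatment day and at 24 weeks.

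**The concern.** One section gives two incompatible schedules for collecting harms, and its text sends the reader to the table for the detail. This is a contradiction in what is stated. It is not a detail that an article leaves to a fuller protocol.

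It matters for four reasons.

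- **Objective.** Objectives {7} names safety together with efficacy, and the Background gives fear of iatrogenic cuff damage as a reason for the trial.
- **Analysis.** Outcomes {20a} under Statistical methods plans a Poisson regression of complications, reported as a manipulation-to-injection rate ratio. That analysis relies on complications being sought in the same way in both arms and at all three hospitals.
- **Transient events.** The complications and adverse events listed in Outcomes {20a} and Safety/harms {22} include post-operative pain and effects on sleep, blood pressure, heart rate and skin. Such events can resolve well before week 24. If patients were asked only at the two marked visits, these events would depend on late recall or spontaneous report.
- **Monitoring.** Formal committee {21a} has the DSMB examine safety data every 3 months, which presupposes that such data arrive between treatment and week 24.

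**Working it through.** No sample size, power or alpha figure is involved. The check is a count of marks in Table 1 set against the text.

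**Step 1: marks by visit, as shown in Table 1**

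| Row | Screening | Treatment day | 1 day | 2 wk | 4 wk | 12 wk | 24 wk |
|---|---|---|---|---|---|---|---|
| Active ROM, passive ROM, CMS, MPQ, VAS, PPI | – | x | x | x | x | x | x |
| Safety evaluation | – | x | – | – | – | – | x |
| Adverse event | – | x | – | – | – | – | x |

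**Step 2: counts.** From treatment day on there are 6 visits. The six efficacy and pain rows are marked at 6 of 6, and each safety row at 2 of 6. Of the 5 post-treatment visits, each safety row is marked at 1 and blank at 5 − 1 = 4. Screening is left out of the count because it precedes treatment.

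**Step 3: is it a column-reading fault?** Each safety row has a label and seven cells, the same as the CMS row, so the columns line up. The six assessment rows use a separate mark for each visit.

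**Step 4: which statement is the outlier?** The timeline text, Safety evaluation and Safety/harms {22} all describe continuing or per-visit recording. Only the two table rows differ.

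**Step 5: consequence if the table were followed alone.**

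- *DSMB.* Three months is about 52/4 = 13 weeks. The interval between the two marked visits is 24 weeks. Since 24 > 13, at least one regular review would fall inside each patient's interval without a scheduled post-treatment safety record.
- *Rate ratio.* Let c_M and c_I be the fractions of true complications captured in the manipulation and injection arms. Then apparent ratio = true ratio × (c_M / c_I). Equal capture leaves the ratio unchanged but reduces the number of events and so the precision. Unequal capture biases it. The document gives no value for c_M or c_I, so no size or direction of bias follows.
- *Sites.* Allocation {16a} stratifies randomization by site in blocks of four, so each hospital has nearly equal arms. If one hospital followed the text and another the table, both arms at each hospital would be affected. That alone mainly costs events and comparability of crude rates between hospitals. Bias in the ratio additionally needs capture to differ by arm.

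**The case against.** The strongest reply is that the collection rule is clear and the table merely fails to repeat it. Besides the three statements above, Modifications {11b} promises safety data for all who leave the study, and Auditing {23} has CRFs checked for completeness every 3 months. Interim analysis {21b} names the standard operating procedure, investigator manual and CRF as working documents. None of these is shown, and nothing says that the CRF is built from Table 1. Data collection {18a} also refers to a figure for the schedule, which is not shown.

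This largely stands. A reader might infer from the table that sites would miss harms at four visits, or that the plan leaves a 24-week gap. The documents do not support that, because the text itself requires recording at those visits. The gap exists only for a site or CRF that follows the table alone.

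A second reply is that the published table may have joined the two marks with a line or arrow lost in text extraction. The row for the two-week exercises is marked only at 1 day and 2 weeks for a daily programme, which suggests that ends of a period can be marked. This cannot be excluded, but it is weak. Those two columns are adjacent, and the other repeated assessments carry a mark at every visit.

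A third reply is that cuff safety is assessed mainly by MRI and ultrasound at 6 months. That imaging is marked at 24 weeks in its own row and is unaffected. This is correct, and it confines the point to clinically reported events.

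**Conclusion.** The contradiction is real: both safety rows are blank at 4 of 5 post-treatment visits, while the text requires recording at each. Confidence in the mismatch is high, subject only to a lost graphic element in the table.

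The consequence is conditional. If a site or the CRF follows the table instead of the text, events between treatment day and week 24 could be captured late or unevenly across sites. That would weaken the complication rate ratio and the DSMB's 3-monthly review.

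A reader might go further and infer a biased rate ratio, for instance because manipulation takes place in an operating room with ward care and the control treatment is an injection. The documents do not support that step. Both arms have the same visits, and any capture fractions would be invented. The point is an internal inconsistency with a modest, unquantified risk. It is worth correcting because the schedule table guides conduct and the correction is nearly free.

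**What to change.** In Table 1, also mark the safety evaluation and adverse event rows at 1 day and at 2, 4 and 12 weeks. Keep the marks at treatment day and 24 weeks, and leave the 24-week MRI and ultrasound in the imaging row. Then check that the CRF has adverse event entries at the same visits, and correct it if it follows the table as shown. If the published table did join the two marks by a line or arrow, replacing it with one mark per visit removes the ambiguity.

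The cost is an edit to two table rows and a check of the CRF pages. Patients already attend all these visits in person (Adherence {11c}), so no visit or examination is added and no treatment rule changes. Because recruitment began on 1 January 2023, sites should also be told that the per-visit rule in the text applies, and should be asked whether any have been recording events only at the two marked visits.

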### Sample size {14}

The total effective rate is the primary outcome parameter. This is based on the efficacy of previous studies on MUA [56] and intra-articular steroid injection [57] in the treatment of FS. The sampling ratio for the treatment and control groups is 1:1, and the number of test subjects required for each group sets as *n*, using a two-sided test. πT and πC are the reference values for the efficacy of previous studies on MUA and steroid substance shoulder cavity injection for FS, respectively [56, 57], setting πT = 0.862 and πC = 0.428. Based on these parameters, we calculated a sample size of 160 subjects per group with a power of 80%, alpha 0.05, and a 10% drop out rate.

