## Trial design {8}

This trial is a randomized, controlled, prospective, multicenter superiority trial with two parallel groups. Patients with FS accompanying MRI diagnoses as rotator cuff injury or tear are randomly divided into two groups: the trial group (with manipulation under brachial plexus block anesthesia as the main intervention) and the control group (with intra-articular steroid injection as the main intervention). All patients included in this study will undergo a program of shoulder exercises, normally commencing within 24 h after the corresponding intervention, with three sessions per day lasting for 2 weeks. The data will be collected before the intervention, 1 day, 2 weeks, 4 weeks, 12 weeks, and 24 weeks after the intervention. Randomization will be performed by a computer-generated random number table with a 1:1 allocation.

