### Recruitment {15}

According to the sample size calculation, this trial requires 320 patients in total. This project uses online media promotion, bulletin board in the hospital, recruits from outpatient visits, and other ways to recruit subjects with stiff shoulders in the Orthopedic Department Outpatients of Shuguang Hospital, Shanghai First People's Hospital, and Shanghai Baoshan District Hospital of Integrated Traditional Chinese and Western Medicine. The participants will undergo two initial diagnostic screenings conducted by clinicians at each research center. The clinicians responsible for diagnosis and screening are unaware of the random grouping. At the scheduled clinical visit, the study clinicians will briefly explain the study to the participants. If interested, the clinicians will assess whether the participant meets the eligibility criteria. If the participant is eligible and agrees to participate, the clinicians will obtain informed consent and enroll the participant. Before signing the informed consent, participants can discuss the study details with the clinicians and ask questions. After enrollment, full-time research assistants will conduct physical and imaging examinations and assign the treatment based on randomization.

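### The stated sample-size inputs give about 18 to 26 patients per group, not 160, so the planned size and the 80% power claim do not follow from the plan's own figures

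*Protocol article*

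**What the plan says.** The protocol article, Sample size {14}, sizes the trial on a single binary endpoint: "The total effective rate is the primary outcome parameter". The assumed rates come from earlier studies of each treatment, "setting πT = 0.862 and πC = 0.428", with T for MUA and C for steroid injection. The other inputs are in the same section: "The sampling ratio for the treatment and control groups is 1:1", and the comparison is made "using a two-sided test". The result is presented as following directly from those inputs: "we calculated a sample size of 160 subjects per group with a power of 80%, alpha 0.05, and a 10% drop out rate".

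Recruitment {15} carries the figure forward: "According to the sample size calculation, this trial requires 320 patients in total". Trial design {8} describes the study as follows: "This trial is a randomized, controlled, prospective, multicenter superiority trial with two parallel groups". No section gives a superiority margin, a design effect, a multiplicity adjustment or a second endpoint as a reason for a larger number.

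**The concern.** A difference of 43.4 percentage points (86.2% against 42.8%) is very large for a binary endpoint and normally needs a few dozen patients in total. A requirement of 320 is out of proportion to it.

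The section gives every input that a two-proportion calculation needs and says that the answer came from them, so the result can be checked directly. If it does not reproduce, at least one of the rates, the power, the size or the hypothesis is misreported. Readers then do not know what effect the trial was designed to detect. Nor can they judge whether 320 people need to be randomized. The Data and Safety Monitoring Board, which under Formal committee {21a} and Interim analysis {21b} reviews effectiveness and may end the trial, would also lack a reliable target effect.

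**Working it through.** **Inputs, all from Sample size {14}:** p_T = 0.862, p_C = 0.428, 1:1 allocation, two-sided alpha 0.05 (z = 1.960), power 80% (z = 0.842), dropout 10%.

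Derived quantities:
- difference d = 0.862 − 0.428 = 0.434, so d² = 0.18836
- V = 0.862 × 0.138 + 0.428 × 0.572 = 0.11896 + 0.24482 = 0.36377
- mean rate = 0.645, so 2 × 0.645 × 0.355 = 0.45795

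**Attempt to reproduce 160 per group**

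1. Unpooled variance: n = (1.960 + 0.842)² × V / d² = 7.849 × 0.36377 / 0.18836 = 15.2, so 16.
2. Pooled variance under the null: n = (1.960 × √0.45795 + 0.842 × √0.36377)² / d² = (1.3263 + 0.5076)² / 0.18836 = 17.9, so 18.
3. Continuity-corrected, starting from the unrounded pooled n: n = (17.86 / 4) × [1 + √(1 + 4 / (17.86 × 0.434))]² = 22.2, so 23.

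| Method | Per group | After 10% dropout (n / 0.9) |
|---|---|---|
| Unpooled | 16 | 18 |
| Pooled | 18 | 20 |
| Arcsine | 18 | 20 |
| Fisher exact (enumerated power 80.8%) | 22 | 25 |
| Continuity-corrected | 23 | 26 |
| **Protocol** | **144** (160 × 0.9) | **160** |

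The ratio to the protocol's figure runs from 160 / 26 = 6.2 to 160 / 18 = 8.9.

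**Stricter inputs do not reach 160 either**

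- Alpha 0.025, as if split over two primary outcomes (the Abstract and Outcomes {12} also name the Constant-Murley Score): 22 per group, or 27 with continuity correction; 25 or 30 after dropout.
- The most demanding combination tried (two-sided alpha 0.01, 99% power, continuity correction): 58 per group, 65 after dropout.

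**Power that the stated size gives at the stated rates**

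z = (d√n − 1.960 × √0.45795) / √V. With n = 144: (0.434 × 12 − 1.3263) / 0.6031 = 6.4, so power is above 99.99%. The same holds with all 160 evaluable.

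**Difference that 144 per group detects with 80% power (pooled formula)**

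- Control rate fixed at 42.8%: MUA rate 59.2%, a difference of 16.4 points.
- MUA rate fixed at 86.2%: control rate 72.9%, a difference of 13.3 points.

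**Superiority margin that would give the stated size**

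The protocol states no margin, so this is an assumption. Solving 7.849 × 0.36377 / (0.434 − M)² = n for M gives M = 0.293 for n = 144 and M = 0.300 for n = 160. The trial would then be testing whether MUA is better by more than about 29 to 30 percentage points.

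**The case against.** The strongest reply is that the mismatch does no harm to the primary comparison. It is towards too many patients, and if the quoted rates are near the truth, 144 evaluable per group is ample. A larger trial may also be reasonable on other grounds: rotator cuff safety on imaging, and the subgroup and imaging analyses that Additional analyses {20b} plans on all 320 patients. This stands as far as it goes. The trial is not underpowered at its stated rates, and nothing here invalidates the analysis. But the protocol gives none of these grounds as the basis for 160. It says that the number came from the two rates.

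A second reply is that an unstated superiority margin is not the only possible explanation. A misprinted rate would do as well: 42.8% against about 59%, or about 73% against 86.2%, fits roughly 144 per group. That is correct. The document does not show which item is wrong, and 80% power may hold for whatever effect was intended. What can be said is that the size, the power and the rates, as printed, are mutually inconsistent.

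A third reply is that replacing the rates with a difference chosen to fit 320 would back-fit a rationale after recruitment began in January 2023. This is fair, and it bears on how the fix is worded.

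Condensation of a full protocol into an article is no answer. The inputs, the result and the link between them are all printed, and the link fails.

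**Conclusion.** The concern holds. From the stated inputs the requirement is 16 to 23 evaluable patients per group, or 18 to 26 after 10% dropout. That is about 36 to 52 in total, against 320 stated. At the stated size, power for the stated rates exceeds 99.99%, not 80%.

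This rests only on the figures printed in Sample size {14} and on ordinary two-proportion tests of no difference between the groups. The choice of formula, rounding and dropout convention moves the answer by a few patients and does not change the conclusion. The margin of 29 to 30 points and the detectable differences of 13 to 16 points show what could lie behind 160. They are not claims about what the sponsor did. The direction is towards more patients than the stated comparison needs, or towards misreported inputs. It must be corrected because the stated basis for the trial's size is wrong as written.

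**What to change.** Amend Sample size {14} so that the rates, hypothesis, power and number agree, and conform Recruitment {15} to it. The sponsor should go back to the calculation that produced 160, report its formula and inputs, and then apply whichever of these is true:

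- If a superiority margin was used, state it, and define the hypothesis and primary test to match.
- If another target drove the size, such as the Constant-Murley Score or cuff safety, name it and give its inputs.
- If a rate was misprinted, correct it.
- If the quoted rates were the planning values and 320 is kept, state that power at those rates exceeds 99.9%. Add the difference that 144 evaluable per group detects with 80% power (for example 42.8% against about 59%). Label it as the sensitivity of the fixed size, not as the planning assumption.

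The cost is a text amendment to the sample-size section. Enrolment, allocation and follow-up need not change. Protocol amendments {25} requires formal amendment and ethics approval for changes to the sample size, so a sponsor who chose to change the number as well would face that larger step.

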### Recruitment {15}

According to the sample size calculation, this trial requires 320 patients in total. This project uses online media promotion, bulletin board in the hospital, recruits from outpatient visits, and other ways to recruit subjects with stiff shoulders in the Orthopedic Department Outpatients of Shuguang Hospital, Shanghai First People's Hospital, and Shanghai Baoshan District Hospital of Integrated Traditional Chinese and Western Medicine. The participants will undergo two initial diagnostic screenings conducted by clinicians at each research center. The clinicians responsible for diagnosis and screening are unaware of the random grouping. At the scheduled clinical visit, the study clinicians will briefly explain the study to the participants. If interested, the clinicians will assess whether the participant meets the eligibility criteria. If the participant is eligible and agrees to participate, the clinicians will obtain informed consent and enroll the participant. Before signing the informed consent, participants can discuss the study details with the clinicians and ask questions. After enrollment, full-time research assistants will conduct physical and imaging examinations and assign the treatment based on randomization.

### Allocation {16a} {16b}{16c}

Eligible subjects who meet the test and research criteria will be randomly assigned into two groups, the trial group and the control group, in a 1:1 ratio. The random number table used for the randomization process is generated by statisticians at Shanghai University of T.C.M. and is not accessible to anyone else involved in the study. The randomization will be stratified by participating site and done in blocks of four. Each subject can only register and be randomized once, and their information cannot be deleted from the database. The clinicians will identify patients with frozen shoulder and confirm their eligibility using a CRF completed by a designated individual in the shoulder team. The recruiting clinician will then contact the statistical staff for randomization. The hospital staff will be informed of the allocation, but not the patient. The patient will be fully informed about the allocated therapy and given an information sheet to review before deciding to consent, which can take up to a week. If the patient does not consent, their reason for not doing so will be briefly recorded in a CRF. Those who consent will complete baseline forms and receive further treatments.

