**Methods:**

A parallel, single-blinded, multi-center randomized controlled trial of 320 patients will be conducted at three hospitals of China. Eligible patients with frozen shoulder and rotator cuff injury or tear diagnosed by MRI will be randomly assigned to, in equal proportions, the manipulation under anesthesia group and the intra-articular steroid injection group via a central randomization system, undergoing a corresponding operation on day one and a sequent physical exercise for 14 days. The primary outcome is the comprehensive efficacy evaluation (total effective rate) and the change of Constant-Murley Score. Outcome assessors and data analysts will be blinded, and participants will be asked not to reveal their allocation to assessors.

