## Methods

### Study setting {9}

This trial is organized and implemented by the Department of Orthopedics and Traumatology of Shuguang Hospital in Shanghai, China, affiliated with Shanghai University of Traditional Chinese Medicine. The research is planned to be completed in three hospitals: (1) Shuguang Hospital Affiliated with Shanghai University of Traditional Chinese Medicine, (2) Shanghai First People's Hospital, and (3) Shanghai Baoshan District Hospital of Integrated Traditional Chinese and Western Medicine. All three hospitals are grade III, class A comprehensive hospitals in Shanghai, China. Shanghai First People’s Hospital is in the city center area, while Shanghai Baoshan District Hospital of Integrated Traditional Chinese and Western Medicine is located in rural areas, and Shuguang Hospital is located between urban and rural areas. All three hospitals in Shanghai are renowned for their departments of orthopedics and traumatology, and Shi's Orthopedics and Traumatology Department of Shuguang Hospital collaborates frequently with the other two hospitals on scientific research projects. By utilizing a practical trial design and involving a broad range of clinicians, the study’s results will be both applicable and generalizable.

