### Blinding (masking)

#### Blinding mechanism {17a}

Due to the nature of the intervention, comparing MUA and intra-articular injection treatment options, it is not possible to blind the clinicians to the allocation of treatment. However, they are strongly advised not to reveal the participant’s allocation status during follow-up assessments. An employee outside the research team will enter data into separate datasheets to ensure that the researchers who are responsible for the analyzation of the data do not have access to the information about allocation. The assessments of clinical recovery will be carried out by an experienced clinician who has undergone extensive training and is blind to treatment allocation.

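### A single fixed block size of four within each site lets anyone tallying that site's allocations foresee up to a third of them, and the allocation section also puts disclosure of the arm before consent

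*Protocol article*

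**What the plan says.** The abstract says patients are assigned "via a central randomization system". Study setting {9} names three sites: "The research is planned to be completed in three hospitals". Allocation {16a} {16b}{16c} assigns patients to "the trial group and the control group, in a 1:1 ratio" and adds: "The randomization will be stratified by participating site and done in blocks of four". It gives one block size and describes no variation. It also says that the list is produced by university statisticians and closed to everyone else in the study.

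On release, the same section says: "The recruiting clinician will then contact the statistical staff for randomization. The hospital staff will be informed of the allocation, but not the patient". Its next sentences nevertheless have the patient fully informed of the allocated therapy, then given up to a week to decide on consent, with reasons for refusal noted on a CRF. Recruitment {15} and Informed consent process {26a} give the opposite order: consent and enrolment come first, after which "full-time research assistants will conduct physical and imaging examinations and assign the treatment based on randomization".

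On blinding, Blinding mechanism {17a} says "it is not possible to blind the clinicians to the allocation of treatment". Recruitment {15} says that the clinicians who diagnose and screen do not know the random grouping, but does not say how this is achieved.

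**The concern.** Concealment requires that whoever decides on entry cannot foresee the next arm. Locking away the list is not enough if the next arm can be deduced from the block size and the arms already given. Here the block size is fixed and short, each site runs its own sequence, and the arms are easy to tell apart (manipulation under nerve block in an operating room, or an injection). The recruiting clinician is the person who requests the allocation.

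If arms can be foreseen, the choice of whom to approach and when can follow the expected arm. The background section supplies a motive: it reports that many physicians are wary of manipulation when MRI shows cuff injury, and exclude such patients. Blinded outcome assessment does not protect against this, because the bias enters at recruitment.

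The consent sequence is a second and more direct route. If the patient and staff know the arm before consent, refusal can depend on the arm and no prediction is needed.

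**Working it through.** The protocol gives no predictability figure, so there is none to reproduce.

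**Inputs.** Block size 4, stratified by site, 1:1 (Allocation); three sites (Study setting); 320 patients ("this trial requires 320 patients in total", Recruitment). The observer is assumed to know the block size and all earlier arms in the site's current block.

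**Certain allocations, fixed fours.** There are C(4,2) = 6 equally likely blocks.
- AABB and BBAA: positions 3 and 4 are certain (2 each).
- ABAB, ABBA, BAAB, BABA: only position 4 is certain (1 each).
- Expected certain allocations per block = (2×2 + 4×1)/6 = 4/3, so the share is (4/3)/4 = 1/3.
- 320 × 1/3 = 106.7, about 107, and slightly fewer if a site ends on an incomplete block.

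**Best guess, fixed fours.** The rule is to guess the arm that is behind at the site. Success by position is 1/2, 2/3, 2/3 and 1. The mean is (17/6)/4 = 17/24 = 70.8%, or 320 × 17/24 = 227 correct, against 160 by chance. This rule needs the tally but not the block size.

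**Alternatives.** The same enumeration was used for fixed sizes. The mixed rows come from simulation (300 sequences of 320) for an observer who knows which sizes are in use but not their order.

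| Block scheme | Certain | Best guess |
|---|---|---|
| Fixed 4 | 33.3% | 70.8% |
| Fixed 6 | 25.0% | 68.3% |
| Fixed 8 | 20.0% | 66.6% |
| Random 4/6 | 5.6% | 69.3% |
| Random 4/6/8 | 2.3% | 68.1% |

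Check on the last row: (4×17/24 + 6×41/60 + 8×373/560)/18 = (2.833 + 4.100 + 5.329)/18 = 0.681.

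**Timing.** Trial status plans recruitment from 1 January 2023 to 31 December 2024. The article appeared on 27 November 2023, so the size was public through it for about 13 of 24 months. If recruitment were even over time and the size unknown at sites before publication (both assumptions), 320 × 13/24 = 173 patients would be exposed, and 173/3 = 58 allocations certain. The upper bound for a full tally is therefore about 58 to 107, depending on when the size became known.

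**Cost in balance.** The worst imbalance per site is half the largest block: 2 for fixed fours, 4 for 4/6/8. Over three sites the latter is 12, a split of 166 to 154. Relative efficiency = 4×166×154/320² = 102,256/102,400 = 0.9986, a loss of 0.14%.

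**Order of consent and allocation.** Allocation runs: eligibility, randomisation, staff told, patient told the therapy, consent or refusal. Recruitment and Informed consent process run: eligibility, consent, enrolment, assignment. Both cannot be followed. No refusal rate is given, so the effect of this route cannot be sized.

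**The case against.** A reader might infer that site clinicians know every past allocation and that a third of the trial is therefore predictable. The documents do not say so. They say that hospital staff are told and that treating clinicians are unblinded, not that each recruiter sees colleagues' patients. Recruitment {15} says that screening clinicians are unaware of the grouping. That stands: one third is an upper bound for someone holding a complete site tally. However, no mechanism supports the statement, and it fits poorly with a recruiting clinician who requests the allocation.

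A reader might also see three competing release routes: a central system, statistical staff contacted by the clinician, and research assistants. These can be read as one loosely worded chain of central list, release on request and local implementation. Only the wording needs tidying.

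There are real safeguards. The list is closed, eligibility is recorded on a CRF by a designated person, patients are randomised once and cannot be deleted, motion limits are numeric, and radiologists make the MRI diagnosis. These limit steering through eligibility. They do not limit whom a clinician approaches, or when.

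Finally, varying the blocks does not make prediction disappear. A recruiter who simply guesses the arm that is behind loses under 3 percentage points (70.8% to about 68%). The gain is the removal of certainty.

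**Conclusion.** The point holds as a weakness the document itself fixes, not as an omission. With fixed blocks of four, up to one third of allocations (at most about 107 of 320) are certain, and 70.8% can be guessed, for an observer who tallies a whole site and knows the block size. With recruiters who do not share information the figures are lower. Before publication, certainty also depends on the size being known at the site, which the documents do not settle. They do not show that steering has occurred, so selection bias is a risk and not an established result.

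The clearer contradiction is the order of consent and allocation. As the allocation section is written, the arm is known before consent, and changing the block size would leave that route open. Both matters should be corrected.

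**What to change.** - **List.** For patients not yet randomised, have the same statisticians generate new within-site lists with block sizes varying at random, for example 4, 6 and 8. Keep the sizes out of site documents and public text.
- **Sequence.** Reconcile the abstract, Recruitment, Allocation and Informed consent process into one order: eligibility recorded, consent signed, then central release of the arm. Remove the statement that the patient learns the allocated therapy before deciding on consent.
- **Screening.** State how screening clinicians are kept unaware of earlier allocations, or drop the claim.
- **Patients already randomised.** State which consent order was used. If allocation came first, report refusals by site and arm; the plan already records the reasons on a CRF.

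The statistical cost is a worst-case imbalance of 4 per site instead of 2, under 0.2% of efficiency. The administrative cost is larger than a new list: Protocol amendments {25} requires a formal amendment for changes to design or study procedures, with funder-level agreement and ethics approval, and this change probably qualifies. Recruitment was planned to end on 31 December 2024, so the list change helps only if it is still open. Correcting the consent sequence in the text is worthwhile either way.
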